## Abstract

**Background: **Mental health of women is adversely affected during pregnancy. Stress and depression during pregnancy negatively impact birthweight and neuro-cognitive development of the fetus. The current crisis due to the COVID-19 pandemic further adds to the stressful situation. Yoga practiced during pregnancy has beneficial effects on improving stress and depression and preliminary evidence suggests that yoga-based interventions can improve immunity. This study aims to examine the feasibility, acceptability, and preliminary efficacy of a
**
Yoga
**-based intervention for maternal
**
M
**ental health and i
**
M
**munity (Yoga-M
_2_) in a rural community in India.

**Methods: **The study design will be a single-blind individual randomized parallel group-controlled pilot trial with 1:1 allocation ratio. Adult pregnant women, with gestational age between 12–24 weeks will be randomly allocated to either the Yoga-M
_2 _group or the Enhanced Usual Care (EUC) group. Participants in the Yoga-M
_2_ arm will attend weekly group yoga sessions for 12 weeks and will be encouraged to practice yoga at home. In the EUC arm, participants will receive a single session of health education. Eligibility of the participants, recruitment, retention-in-care, and study completion rates will be estimated and feasibility of delivering Yoga-M
_2 _and acceptability of this intervention by the participants will be assessed. Change in the scores of the Perceived Stress Scale (PSS), EuroQoL 5 Dimensions Score (EQ-5D-5L), Wisconsin Upper Respiratory Symptom Severity Scale (WURSS-21), and serum C-Reactive Protein at three-months from baseline will be used to assess preliminary efficacy.

**Discussion:** The key outputs of this trial will be a structured intervention manual and evidence about the feasibility, acceptability, and preliminary efficacy of the intervention, establishing the foundation to undertake an explanatory randomized controlled trial to assess efficacy and cost-effectiveness of Yoga-M
_2_ intervention.

**Trial registration: **
CTRI/2022/01/039701. Prospectively registered with the Clinical Trials Registry of India on 25 January 2022.

## Introduction

### Background

The experience of pregnancy can be both exciting and challenging for a woman and her family. Pregnancy is associated with happiness
^
1
^ and increase in mental aspect of quality of life
^
2
^. However, it can also be a period of increased physical and psychological vulnerability. Changes in cardiorespiratory and immune system functioning increase the susceptibility of women to severe infection and hypoxic compromise
^
3
^. This is especially important during the ongoing COVID-19 crisis as COVID-19 during pregnancy can increase the risk of preeclampsia, venous thromboembolism, premature fetal membrane rupture, or preterm delivery
^
4,
5
^. Women living in social adversity can experience mental health conditions, especially depression which is quite common during this period. One in four women in South Asia is likely to have depression during pregnancy, while in India, the pooled prevalence of antenatal depression is 17.7% (95% CI: 11.2%–26.9%)
^
6
^. Antenatal depression is associated with higher risk of pregnancy-related mortality and morbidity, pre-term delivery, low birth-weight, post-partum depression and adverse neuro-cognitive developmental outcomes in infants, children and adolescents
^
7
^.

Yoga is a mind-body practice, and its roots can be traced in ancient Indian philosophy. Yoga has been practiced in India for more than 7000 years
^
8
^. Yoga during pregnancy can be very helpful in prevention and treatment of stress and depression
^
9
^. A meta-analysis found a positive effect of yoga on antenatal depression
^
10
^. Another systematic review assessing the effect of yoga on immune system functioning found that yoga can down regulate pro-inflammatory markers and enhance cell-mediated and mucosal immunity. This makes yoga a suitable intervention for individuals suffering from diseases with inflammatory component and those who are at higher risk of getting infections
^
11
^. There is only one study which has assessed the effect of yoga on immune function during pregnancy
^
12
^. In this study, yoga-based intervention, which included postures, deep breathing, guided imagery, and deep relaxation was delivered to 48 women during pregnancy, 70 minutes per session, 2 sessions per week for 20 weeks. Pregnant women who practiced yoga had higher immunoglobulin A levels and lower salivary cortisol levels immediately after a yoga session, compared to those who did not practice yoga. In the long-term, salivary immunoglobulin A levels were significantly higher in the yoga group compared to the control group
^
12
^.

How to assess the effect of yoga on inflammatory process is a key question. C-Reactive Protein (CRP) is a nonspecific maker of inflammatory process, the serum levels increase with body insult, tissue damage, aging, and cardiovascular diseases. Bacterial (or viral, fungal) infections lead to a marked increase in serum CRP levels. Although it is not a diagnostic marker, it can be used to track the inflammatory process, overall wellness, and individual’s quality of life. Lifestyle changes such as cessation of smoking, increasing physical activity, reducing body mass index led to a decrease in serum CRP levels
^
13
^. Yoga and other mind-body techniques reduce inflammation through a reduction in CRP
^
14
^. An eight week Hatha yoga program compared to standard medical treatment was found to significantly reduce serum concentrations of interleukin 6 and CRP in two randomized controlled trials
^
15,
16
^.

### Rationale for study

The possibility of another COVID-19 wave in India (and other parts of the globe) can’t be entirely ruled out. This necessitates generating evidence for population-based interventions which can improve immune system functioning and reduce the susceptibility of infections in vulnerable groups like pregnant women. Yoga can be practiced by pregnant women as self-care with minimal training. Yoga can play an important role in reducing stress and improving well-being of pregnant women. However, there are no studies from India which have assessed the effects of yoga-based intervention on immune system functioning in pregnant women.

### Objectives

The overall aim of this pilot randomized controlled trial is to examine the feasibility, acceptability, and preliminary efficacy of a
**Yoga**-based intervention to improve maternal
**M**ental health and i
**M**munity (Yoga-M
_2_).

The primary objectives of this randomized pilot trial are:

1. To estimate participant eligibility, recruitment and retention-in-care and study completion rates.

2. To assess the feasibility of delivering Yoga-M
_2 _and acceptability of this intervention by the participants.

3. To assess the preliminary efficacy of Yoga-M
_2 _to improve maternal mental health and immune function.

**
Trial design
**

Single-blind individual randomized parallel group-controlled pilot trial with 1:1 allocation ratio.

## Methods

This protocol follows the Standard Protocol Items: Recommendations for Interventional Trials (SPIRIT) guidelines
^
17
^. The SPIRIT checklist is uploaded as extended data
^
18
^.

### Research ethics approval

This study is approved by the Institutional Ethics Committee of the Pravara Institute of Medical Sciences (Approval Number: PIMS/DR/RMC/2020/225).

### Study setting

The study will be carried out in villages close to Pravara Institute of Medical Sciences (PIMS) in Rahata taluka of Ahmednagar district in Maharashtra, India. Rahata is one of the 14 administrative blocks (taluka) in Ahmednagar district with a total population of 320,485, out of which 81.8% is rural as per the
2011 census. PIMS has a tertiary care center with a 1275 bedded multi-disciplinary facility and is located in Loni Budruk village. The antenatal clinic of the Department of Obstetrics and Gynecology provides services to approximately 150–200 pregnant women every day. This study will recruit pregnant women from four neighboring villages: Loni Khurd, Loni Budruk, Kolhar Budruk, and Kolhar-Bhagwatipur. 

### Eligibility criteria

We will first enlist all pregnant women in the study villages with the help of Anganwadi workers. We will then invite women with a gestational age between 12 weeks to 24 weeks for small group meetings in the Anganwadi centers to explain to them the proposed study. Anganwadi is a community-based center providing healthcare check-up and referral health services, supplementary nutrition, immunization, and non-formal pre-school education. Expectant and nursing mothers, children, and adolescent girls are the primary beneficiaries. These centers were established as part of the Integrated Child Development Service (ICDS) and are managed by female community health workers called Anganwadi workers. Each center caters to a population of approximately 1000 people in rural areas. Anganwadi workers have an updated list of all pregnant women in their respective areas. Pregnant women who are interested in participating in the study will be requested to attend the antenatal clinic of the Department of Obstetrics and Gynecology, PIMS. An eligibility assessment form will be completed by a trained Research Assistant (RA) in the antenatal clinic followed by a complete clinical examination by their obstetrician. The following inclusion/exclusion criteria will be used to assess the eligibility:

**
Inclusion criteria:
**

-Adult pregnant women above 18 years of age-Gestational age between 12–24 weeks-Planning to stay in the study area (described above) throughout study duration (approximately four months)

**
Exclusion criteria:
**

-Pregnant women advised rest by their obstetrician due to medical/obstetric problems-History of two or more spontaneous abortions-Inability to communicate in Marathi language-Inability to attend yoga sessions-Receiving treatment for depression or any other mental health condition-Practicing yoga regularly for at least once a week since last four weeks

### Informed consent

A participant information sheet will be given to all eligible participants. The information sheet will include the details about the purpose of the trial, various study procedures, and contact details of the Principal Investigator and the Member Secretary of the Institutional Ethics Committee. An audio-visual version of this participant information sheet will be uploaded on the project
website and the participants will be informed about how to access this. Sufficient time will be given to participants to read the information sheet and to ask any questions about the trial. They will be then invited to participate in the study. 

Eligible participants who agree to participate in the study will provide informed written consent by completing a hard copy of the consent form (see
*Extended data*
^
17,
18
^). Prior to signing the consent form, participants will have opportunity to review the form and ask questions about the study. Participants who are illiterate (not able to read and write Marathi, but can communicate in Marathi), will provide a verbal consent (audio-recorded) after the RA reads out the information sheet to them. An impartial third party (a family member or a health care worker) will witness the consent process and will sign the consent form.

A separate written informed consent will also be obtained at three-month follow-up assessment, for the qualitative study and for the recording (audio/video) of yoga sessions to assess fidelity and quality of intervention delivery.

RAs will be trained to ensure that the purpose of the study, randomization and other study procedures are adequately explained, and the informed consent is appropriately obtained. They will be required to sign the consent forms as well.

A copy of the participant information sheet and the informed consent form will be handed over to the participants. Those who decline to participate will be asked the reason for refusal and with their permission, their age, education, occupation, and religion will be recorded. Refusals at three-month follow-up will also be recorded.

**
Additional consent provisions for collection and use of participant data and biological specimens
**

The consent form will have a specific item for collection of the blood sample at the time of baseline and three-month follow-up assessment. Five milliliter of blood will be collected at baseline and at three-month follow-up to measure the level of serum C-Reactive Protein. It will ask the participants consent to share the anonymized data with other researchers and to use the anonymized data to support other research in the future.

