### Interventions

**
Intervention arm: Yoga-based intervention for maternal Mental health and iMmunity (Yoga-M
_2_)
**

Participants randomized to the intervention arm will attend weekly supervised group yoga sessions and will also be requested to practice yoga regularly at home for a total duration of three-months. Group yoga session will be for 60 to 75 minutes. A typical session will begin with an introduction of the participants, a brief overview of the session by the yoga instructor and an opening prayer. This will be followed by
*sukshma-vyayam* (micro-circulation exercises) for 10 minutes,
*asanas* in standing, sitting, and supine position for 15 minutes,
*pranayama* for 15 minutes followed by
*shavasana* (deep relaxation) for 10 minutes. The session will end with a closing prayer. A detailed description of the yoga session is provided in
Table 1. After the session ends, the yoga instructor will spend time with each participant individually and suggest changes/modifications based on any problems they might have in practicing any of the yoga-based activities. Weekly group sessions will be conducted either in-person or online. In-person sessions will be preferred if allowed, depending on the COVID-19 pandemic-situation in the study area and restrictions in place. In-person sessions will be in a well aerated and ventilated hall. Use of sanitizers where appropriate and physical distancing will be maintained during yoga sessions. Participants can also attend group yoga sessions online via
Zoom. The plan is to have five in-person group yoga sessions over five days in the beginning to teach the entire yoga sequence to the participants. This will be followed by weekly group yoga sessions. We anticipate that each participant will attend 10 group yoga sessions over 12 weeks.

**Table 1. T1:** Yoga-based intervention for maternal Mental health and iMmunity (Yoga-M
_2_).

	Type of Activity	Duration (Second Trimester)	Duration (Third Trimester)
**1.**	**Opening Prayer** ‘Om, Sahana Vavatu Sahana Bhunattu Saha Viryam Karawavahai Tejasvinavaditamastu Ma vidvishavahai Om, Sāntih Sāntih Sāntih’	**3 minutes**	**3 minutes**
2.	** *Sukshma-Vyayam* ** **(Micro-circulation exercises)**	**10 minutes**	**5 minutes**
	*Griva Sanchalan* Neck movements	Yes	Yes
	*Skandha Paribhraman* Shoulder rotation	Yes	Yes
	*Hasta Ayama Svasanam* (Hands in and out breathing)	Yes	Yes
	*Hasta Vistara Svasanam* (Hands stretch breathing)	Yes	Yes

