_2_ intervention. A few modifications in the sequence for individual participants may be done by the yoga instructor based on feedback from them. Obstetrician may advise participants to discontinue yoga due to health issues or they may decide to stop practicing yoga themselves for any reason.

**
Strategies to improve adherence to interventions
**

The IC and the yoga instructor will regularly contact participants in Yoga-M
_2_ arm to coordinate attendance in weekly group yoga sessions. If a participant misses two consecutive weekly group yoga sessions, the IC will visit the participant at home to address any barriers related to joining the session. Adherence to home practice will be assessed using home practice logs. 

**
Relevant concomitant care permitted or prohibited during the trial
**

Throughout the duration of the trial, participants will receive usual care and no specific component of antenatal care or other health services will be prohibited.

**
Provisions for post-trial care
**

Participants in both arms will receive information about yoga classes they can join after the end of the trial. Participants in the control arm will also receive the yoga intervention booklet and the audio-visual material. Participation in yoga classes post-trial will be entirely voluntary and on a self-pay basis. No compensation will be provided to participants who suffer non-negligent harm from trial participation.

**
Outcomes
**

Outcome assessment will include measures related to:

a) feasibility and acceptability of yoga-based intervention (Yoga-M
_2_) deliveryb) preliminary efficacy of Yoga-M
_2_

Feasibility and acceptability will be assessed using the following process data:

1. Number and proportion of eligible participants who are recruited per week in each arm.2. Number and proportion of recruited participants in Yoga-M
_2_ arm who attend the in-person yoga sessions.3. Number and proportion of recruited participants in Yoga-M
_2_ arm who attend at least 50% of the follow-up yoga sessions.4. Number and proportion of recruited participants who complete follow-up assessment three-months post-randomization in each arm.

Process data will be collected from the study enrollment logs and intervention delivery logs. Study enrollment logs will be maintained by RAs and intervention delivery logs will be maintained by the IC. Every week this data will be manually entered and stored as CSV files on an access-restricted computer.

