### Data collection and management

**
Plans for assessment and collection of outcomes
**

Case Record Forms (CRF) will be used by RAs to collect data at baseline and at three-months follow-up assessment. Both the baseline and follow-up assessment will be completed in the antenatal clinic of the Pravara Institute of Medical Sciences. Pen and paper format will be used for data collection. Data will be converted into digital format by manual entry using
Microsoft Excel. Data will be stored as a CSV (comma-separated values) file. There will be a date and time stamp of the original data entry and any subsequent change to the document will be noted in an audit trail. Data related to the fidelity and quality of yoga intervention delivery will also be in paper form and similar process will be used to enter and store data as a CSV file. Digital voice recorders will be used to collect qualitative data. A document containing memos and field notes will be maintained. The audio data will be transcribed in Marathi and then translated in English for analysis. The data will be anonymized but linked with the trial ID.

For each data source, the CRC will perform the data, range, and consistency checks at weekly intervals. The CRC will resolve the queries promptly and will update the database and maintain the audit trail. Initially, separate databases will be used to store different types of data. Once the data collection is complete, each individual database will be locked, and these separate databases will be merged into a master. Passwords will be used by the CRC to protect the data. No member of the trial team will have access to these passwords.

**
Plans to promote participant retention and complete follow-up
**

At the baseline, participants will be informed about the three-month follow-up assessment and an interview will be scheduled coinciding with their antenatal check-up. A reminder phone call will be made one week prior to the follow-up assessment. A seven-day window period after the due date will be allowed to complete the assessment. In case the participants are unable to visit the antenatal clinic, a home-visit will be planned as per the convenience of the participant.

**
Data management
**

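### Consent to record yoga sessions for fidelity rating is timed at the three-month visit, when few or no sessions are left to record

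*Protocol article*

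**What the plan says.** All references are to the protocol article.

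- **Consent.** Informed consent states: "A separate written informed consent will also be obtained at three-month follow-up assessment, for the qualitative study and for the recording (audio/video) of yoga sessions". The purpose given for the recording is "to assess fidelity and quality of intervention delivery".
- **Course.** The Abstract says that women in the Yoga-M2 "arm will attend weekly group yoga sessions for 12 weeks and will be encouraged to practice yoga at home". Interventions says that they attend weekly supervised sessions and "practice yoga regularly at home for a total duration of three-months". It adds: "The plan is to have five in-person group yoga sessions over five days in the beginning", with weekly sessions after that. On attendance it says: "We anticipate that each participant will attend 10 group yoga sessions over 12 weeks".
- **Follow-up visit.** Outcomes counts the "recruited participants who complete follow-up assessment three-months post-randomization in each arm", and Table 3 gives the same time point. The section on retention and complete follow-up allows seven days after the due date and none before it.
- **Fidelity data.** Data collection and management confirms that such data are planned: "Data related to the fidelity and quality of yoga intervention delivery will also be in paper form".

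No earlier consent for recording sessions appears in the article. The specific consent-form items that it describes are blood sampling and the sharing and reuse of anonymised data. The audio recording mentioned at enrolment concerns the verbal consent of women who cannot read and write Marathi, not the yoga sessions.

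**The concern.** Consent to record has to come before the recording. The article places it at a visit that falls at or after the end of the activity to be recorded. The time phrase in the consent sentence stands before both purposes, so on a plain reading it governs the recordings as well as the qualitative interviews.

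A team following the text has two options. It can wait for consent, and then few or no sessions are left to record. Or it can record during the course and ask afterwards, and then women are recorded before they have agreed. The first option empties the only source of fidelity data that the article names. The second reverses the order of consent. This is a time point that the article states and that defeats its own purpose, so it is not a detail left to a fuller document.

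**Working it through.** The plan gives no figure to reproduce, so the check is a calendar count with day 0 as randomisation.

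**Inputs from the article**
- Five teaching sessions over five days at the start, then weekly sessions (Interventions).
- Course length of 12 weeks, 12 × 7 = 84 days (Abstract).
- Visit at three months after randomisation (Outcomes, Table 3), taken as day 91 (13 weeks) or day 92 (calendar months).
- Window of up to seven days later (retention section): 91 + 7 = 98 or 92 + 7 = 99.

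**Assumptions**
- The lag L from randomisation to the first session is not stated. I take 0 to 28 days.
- The 12 weeks may include the opening week or follow it. Both readings are shown.

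**Session days**
- Opening sessions: days L + 1 to L + 5.
- Weekly sessions: day L + 5 + 7k, for k = 1, 2, …, K.
- Reading A, weekly sessions up to day 84 of the course: K = 11, in total 5 + 11 = 16 sessions, the last on day L + 5 + 77 = L + 82.
- Reading B, 12 further weekly sessions: K = 12, in total 5 + 12 = 17 sessions, the last on day L + 5 + 84 = L + 89.

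The sessions left after a visit on day F are those with L + 5 + 7k > F. For example, with L = 14 and F = 91 the condition is 7k > 72, so k ≥ 11. That leaves one session under A and two under B.

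**Sessions left after the visit (reading A / reading B)**

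| Lag L (days) | Visit on day 91 or 92 | Visit on day 98 or 99 |
|---|---|---|
| 0 | 0 / 0 | 0 / 0 |
| 7 | 0 / 1 | 0 / 0 |
| 14 | 1 / 2 | 0 / 1 |
| 21 | 2 / 3 | 1 / 2 |
| 28 | 3 / 4 | 2 / 3 |

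**Sensitivity.** If three months is read as exactly 84 days, 0 / 1 session is left with no lag and 4 / 5 with a lag of 28 days.

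**Opening sessions.** Even with L = 28 they end on day 28 + 5 = 33, well before any of these visit days.

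**Staggered recruitment.** It does not rescue the schedule. Women attending a session are still in their course and, under the written rule, have generally not yet reached the visit at which they would consent.

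**If consent came before the first session**, all 16 or 17 scheduled sessions could be recorded with prior consent.

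**The case against.** **The sentence may be a slip of condensation.** The three-month timing suits the qualitative interviews, and the authors may not have meant it for the recordings. The consent forms are listed as extended data, are not shown here, and could settle what was intended. This stands as a doubt about intent and about what will happen in practice. It does not change what the sentence says, and nothing else in the article corrects it.

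**A delayed start is plausible.** The inclusion criteria put study duration at approximately four months, which leaves room around a 12-week course. This stands too: it would be wrong to say that no session could ever be recorded with consent. With a lag of 2 to 4 weeks a few late sessions remain, though never the opening block that teaches the sequence.

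**The consequences are easy to overstate.** A reader might infer more than the article supports:

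- *That the feasibility objective fails, or that a null result could not be told apart from poor delivery.* Outcomes assesses feasibility and acceptability by recruitment, session attendance and completion of follow-up, and adds a satisfaction survey and interviews with instructors and participants. None of these needs recordings, and recording-based fidelity is not a listed outcome. In a 50-woman pilot with an anticipated effect of 0.2, a null efficacy result would say little with or without recordings.
- *That one refusal spoils a whole group recording, so that the rated sessions favour groups with full retention.* The article sets no such rule. The object of rating is delivery, and audio-only use or masking is not excluded.
- *That women will be recorded without consent.* The article does not plan this. It is one of two ways in which the written rule could play out.

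**Conclusion.** The point holds as a stated timing that conflicts with the course schedule. With sessions starting at or near randomisation, none of the 16 or 17 scheduled sessions falls after a visit on day 91 or 92. With an assumed lag of 2 to 4 weeks, about 1 to 4 late sessions remain if the visit is on its due date, and 0 to 3 if it falls at the end of the window. The five opening sessions are never covered.

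The damage is confined to the recording-based assessment of fidelity and quality, and to the order of consent if recordings are made during the course. The size rests on the unstated start lag and on reading three months as 91 or 92 days. The conclusion for the opening sessions does not depend on either within the range examined. The correction is worth making because it is almost free and concerns consent, not because any estimate in the trial is at risk.

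**What to change.** In Informed consent, split the sentence. Keep the qualitative-study consent at the three-month visit, and state that consent for audio or video recording is obtained before the first recorded session. Either of two routes would work:

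- an optional item on the baseline consent form; or
- consent taken by the Intervention Coordinator from Yoga-M2 women after allocation. The coordinator already knows the allocation, so this adds no task for the blinded Research Assistants.

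If the consent forms already provide for earlier consent, only the published sentence needs correcting.

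The cost is one sentence and one form item, with no extra staff or visits. The downside is that some women may decline, which may limit which sessions can be recorded.
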